## Abstract

**Background:**

Since the beginning of the COVID-19 pandemic, the world’s attention has been focused on better understanding the relation between the human host and the SARS-CoV-2 virus, as its action has led to hundreds of thousands of deaths.

**Objective:**

In this context, we decided to study certain consequences of the abundant cytokine release over the innate and adaptive immune systems, inflammation, and hemostasis, comparing mild and severe forms of COVID-19.

**Methods:**

To accomplish these aims, we will analyze demographic characteristics, biochemical tests, immune biomarkers, leukocyte phenotyping, immunoglobulin profile, hormonal release (cortisol and prolactin), gene expression, thromboelastometry, neutralizing antibodies, metabolic profile, and neutrophil function (reactive oxygen species production, neutrophil extracellular trap production, phagocytosis, migration, gene expression, and proteomics). A total of 200 reverse transcription polymerase chain reaction–confirmed patients will be enrolled and divided into two groups: mild/moderate or severe/critical forms of COVID-19. Blood samples will be collected at different times: at inclusion and after 9 and 18 days, with an additional 3-day sample for severe patients. We believe that this information will provide more knowledge for future studies that will provide more robust and useful clinical information that may allow for better decisions at the front lines of health care.

**Results:**

The recruitment began in June 2020 and is still in progress. It is expected to continue until February 2021. Data analysis is scheduled to start after all data have been collected. The coagulation study branch is complete and is already in the analysis phase.

**Conclusions:**

This study is original in terms of the different parameters analyzed in the same sample of patients with COVID-19. The project, which is currently in the data collection phase, was approved by the Brazilian Committee of Ethics in Human Research (CAAE 30846920.7.0000.0008).

**Trial Registration:**

Brazilian Registry of Clinical Trials RBR-62zdkk; https://ensaiosclinicos.gov.br/rg/RBR-62zdkk

**International Registered Report Identifier (IRRID):**

DERR1-10.2196/24211

## Introduction

COVID-19 emerged in the city of Wuhan, Hubei, China and spread worldwide over the next several months [1]. Originally reported by the World Health Organization (WHO) as a pneumonia outbreak of undetermined origin, COVID-19 had its epidemiological status revised by the WHO as a Public Health Emergency of International Concern by the end of January 2020 and as a pandemic at the beginning of March 2020 [2]. The etiologic agent was identified as a new coronavirus of the *Betacoronavirus* genus, named SARS-CoV-2, due to its structural similarity to severe acute respiratory syndrome–related coronavirus (SARS-CoV), which also accounted for an outbreak in China in 2002-2003 [3]. The disease is characterized by fever, cough, and dyspnea, and can progress to pulmonary failure and lead to liver, heart, and kidney damage. Clinical management of severe cases requires respiratory assistance [4].

Angiotensin converting enzyme-2 (ACE2) mediates SARS-CoV-2 (and other coronaviruses) entry via clathrin-mediated endocytosis into type-2 pneumocytes and macrophages of the lung milieu [5,6]. ACE2 is a membrane-bound enzyme that converts active angiotensin II to inactive angiotensin (1-7). Thus, ACE2 blocks the unfavorable effects of angiotensin II action, including classic vasoconstriction in addition to inflammation and thrombosis. SARS-CoV-2 binding markedly impairs ACE2 catalytic activity by competitive inhibition, with increased in situ pulmonary inflammation and coagulation as detrimental outcomes of weakened counter regulation of the angiotensin II/AT1 receptor axis [7].

Hence, COVID-19 resembles a hyperimmune syndrome defined by potentially lethal hypercytokinemia due to overproduction of a set of proinflammatory mediators, including interleukins (IL-1β, IL-2, IL7), granulocyte colony stimulating factor, interferon-gamma (IFN-γ), monocyte chemoattractant protein-1 (MCP-1), and tumor necrosis factor-alpha (TNF-α), which culminates in multi-organ failure [8,9]. In addition, the Th17-type response plays an important role in severe cases due to an additional proinflammatory overflow resulting from supraphysiological IL-1β, IL-6, and TNF-α levels that contribute to edema formation [10]. The role of cortisol and prolactin in the modulation of the immune system has long been described [11,12], but their participation (if any) in the COVID-19–related “cytokine storm” remains unknown. Moreover, given the intimate interplay of inflammation with blood clotting, severe patients usually show a hypercoagulable profile that leads to an increased frequency of pulmonary thromboembolism, deep vein thrombosis, and even heart and brain ischemia events [13,14].

In this context, it is also no surprise that the first treatment that reduced COVID-19 mortality, in a large randomized controlled trial (RECOVERY [Randomised Evaluation of COVID-19 Therapy]) [12,15], was dexamethasone, a corticosteroid [12]. However, it also showed that the effect seems to depend on the clinical stage of the disease, highlighting the need for further investigations into the course of the inflammatory response. Other anti-inflammatory treatments such as tocilizumab, an IL-6 receptor-blocking humanized antibody used to treat rheumatoid arthritis, were used (out of compassion) in patients with severe COVID-19 in China and Italy [16-18], with some clinical improvement. Similarly, another drug under evaluation is baricitinib, a JAK2 inhibitor approved for myeloproliferative neoplasms and rheumatoid arthritis that reduces Th17-type cytokine secretion by blocking AP2-associated protein kinase 1 [19]. However, the clinical efficacy of baricitinib against COVID-19 has yet to be proven. These studies support the assumption that a cytokine “storm” not only plays a role in COVID-19 pathophysiology but also has predictive prognostic value to monitor the evolution of mild and severe cases.

New metabolomics protocols can characterize metabolic pathways and provide a broad view of the impact of SARS-CoV-2 on the body. Both metabolome and proteome composition are dynamic and reflect genome expression under specific conditions [20-22]. Furthermore, these innovative combination protocols can help in understanding the metabolic profile of a given patient or group of patients [23] from urine, saliva, and blood samples [24]. The chemical profile substantially contributed to biological and medical research, leading to advancements in clinical medical practice [23].

This paper describes the design and rationale of a multicenter prospective cohort study aimed at evaluating the molecular and cellular immune signature of COVID-19 by assessing serum inflammatory mediators and regulatory chemokines of Brazilian patients with different clinical forms of the disease.

## Methods

### Study Design and Population

TARGET is registered in the Brazilian Clinical Trials database with registry code RBR-62zdkk and constitutes a multicenter, prospective cohort study of consecutive COVID-19 cases, consisting of participants recruited from secondary and tertiary health care facilities in Brazil, namely, the University Hospital of Brasília (University of Brasília [UnB]) and the public regional hospitals of Asa Norte, Gama, Santa Maria, and Taguatinga (Brasília, Distrito Federal). Clinical procedures will be conducted according to a standard protocol approved by local institutional review boards under accession number CAAE 30846920.7.0000.0008, with participants included after voluntary signing of an informed consent form. The study protocol follows the recommendations of the STROBE (Strengthening the Reporting of Observational Studies in Epidemiology) statement for observational studies [16].

### Recruitment

Inclusion criteria will include the following: laboratory confirmation of COVID-19 by reverse transcription polymerase chain reaction (RT-PCR; KIT Molecular SARS-CoV2 [E/RP]; Bio-Manguinhos), a signed informed consent form, and older than 18 years. The exclusion criteria are as follows: patients with inconclusive, unavailable, or solely serological laboratory diagnosis of COVID-19; a dementia condition (Alzheimer, Parkinson, vascular frontotemporal, Lewy body, or others); schizophrenia or schizoaffective disorders with psychotic characteristics; and patients with previously known congenital hemorrhagic diseases or thrombophilia or use of anticoagulants (for coagulation tests; Figure 1).

**Figure 1 figure1:**
[figure not shown]
Inclusion and exclusion criteria flowchart. The T-branch group is patients referred to the emergency room with mild or moderate forms of COVID-19 not requiring hospitalization. The D-branch group is patients referred to the emergency room with severe or critical forms of COVID-19 requiring hospitalization.

### Clinical Assessment Protocol

The clinical evaluation aims to identify the signs and symptoms associated with COVID-19 and monitor the status (mild/moderate or severe/critical) of the disease. Clinical assessments include identification of comorbidities, COVID-19–associated symptoms and treatment, use of medications in general, clinical chemistry findings, and life support regimen care. Severe cases are defined for the purposes of the study by dyspnea (respiratory rate >30 breaths per minute) coupled with any of the following criteria: pulsed wave oxygen saturation <93% at rest, PaO_2_/FiO_2_ ≤300 mmHg, respiratory failure requiring mechanical ventilation, multiple organ failure, shock, or admission to the intensive care unit. Patients who do not meet the criteria for severe/critical forms will be considered mild/moderate cases. No asymptomatic patients will be included (Textbox 1 and Table 1).

Components being assessed for characterization of the following domains: symptoms, comorbidities, treatments, biochemical profile, immune biomarkers, and leukocyte phenotype and functionality in the TARGET protocol.

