### Timeline

The TARGET protocol comprises two arms, referred to as the timeline (T)-branch and the days of hospitalization (D)-branch. For the purposes of this study, the T-branch refers to patients with mild/moderate forms that did not require hospitalization. The D-branch refers to patients with severe/critical forms who required hospital admission. Patients on the T-branch will be analyzed on days 0, 9, and 18 (T0, T9, and T18), while patients on the D-branch will be analyzed on days 0, 3, 9, and 18 (D0, D3, D9, and D18; Figure 1).

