**Figure 2 figure2:**
[figure not shown]
Timeline showing the times of blood tests and the analysis performed. The upper line represents the duration of symptoms, a parameter used in the group of patients enrolled for prospective follow-up, composed primarily of patients who will evolve with mild conditions. The lower line represents the blood test dates in the hospitalized group: patients who have already entered the study with moderate to severe conditions, usually from the fifth day of symptom onset.

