### Sample Size Calculation

The sample size calculation was based on the assumption that 20% of patients who are critically ill have elevated TNF-α levels compared to 5% of patients who are noncritically ill [8]. TNF levels will be normalized according to the study population. Based on a bilateral 95% significance level, a power of 80%, and a case-control ratio of 1, a sample size of 200 patients can be predicted.

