### Statistical Analysis

Clinical and demographic data between groups of patients (severe vs nonsevere) as well as treatment profiles and differences in successive time points will be compared. To compare mean values of soluble biomarkers between groups, the *t* student test (or analysis of variance with post hoc test for multiple groups) or the nonparametric Mann-Whitney (or Kruskal-Wallis for multiple groups) test will be used as appropriate, according to the observed sample distribution features. The SAS 9.3 software (SAS Institute Inc) will be used with a significance level set at .05. The main binary outcomes will be analyzed by the estimation of relative risks using a log-binomial generalized model or by the area under the curve using trapezoidal methods. All personnel conducting laboratory procedures will be blinded regarding the patient status (severity of COVID-19). Receiver operating characteristic curves will determine cutoff points at which individual or combined scores of the molecular and cellular biomarkers become informative of the progression of COVID-19 cases, according to optimal sensitivity and specificity to identify the signature that best characterize each clinical status.

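### As worded, the severity rule makes a respiratory rate above 30 mandatory, so some ventilated, shocked or ICU patients default to mild/moderate, and the protocol does not say whether this rule or the T/D branch forms the analysis groups

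*Protocol article*

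**What the plan says.** All of the following is in the protocol article.

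- **Clinical Assessment Protocol.** Severe cases are defined for study purposes "by dyspnea (respiratory rate >30 breaths per minute) coupled with any of the following criteria". The list is oxygen saturation below 93% at rest, PaO2/FiO2 of 300 mmHg or less, and "respiratory failure requiring mechanical ventilation, multiple organ failure, shock, or admission to the intensive care unit". A catch-all follows: "Patients who do not meet the criteria for severe/critical forms will be considered mild/moderate cases".
- **Timeline** (and the Figure 1 legend, to the same effect). "the T-branch refers to patients with mild/moderate forms that did not require hospitalization". "The D-branch refers to patients with severe/critical forms who required hospital admission".
- **Figure 2 legend.** The hospitalized group is described as "patients who have already entered the study with moderate to severe conditions".
- **Metabolomic Profiling.** Mild is equated with the T-branch and severe with the D-branch.
- **Statistical Analysis.** The comparison is "Clinical and demographic data between groups of patients (severe vs nonsevere"), with no statement of which of these definitions makes the groups.
- **Sample Size Calculation.** The assumption is that "20% of patients who are critically ill have elevated TNF-α levels compared to 5% of patients who are noncritically ill", with two-sided testing, 80% power, a 1:1 ratio and 200 patients in total.

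**The concern.** The wording joins one compulsory element, a respiratory rate above 30, to a list from which any one item completes the definition. No item on the list is enough alone, not even mechanical ventilation, shock or ICU admission. Because the catch-all sends everyone else to mild/moderate, a critically ill patient with a rate of 30 or less is labelled with the mildest cases. The branch definitions point elsewhere, since they attach severe disease to hospital admission.

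The severe versus nonsevere contrast underlies the sample size, the group comparisons of biomarkers and the ROC cutoffs. If critically ill patients enter the comparator, differences between groups would tend to shrink and the reference classification for the ROC curves would be contaminated. If the grouping rule is left open, it can be settled after the data are seen, and the two candidate rules can give different results from the same patients.

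**Working it through.** **Step 1. The rule as logic.** Let R = respiratory rate above 30, and C = at least one listed criterion.

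- Severe = R and C.
- Mild/moderate = not (R and C) = (not R) or (not C).

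A patient with C true (for example, in shock) and R false is mild/moderate. Nothing elsewhere in the article makes R optional.

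**Step 2. The same patient under each section.** Take a hospitalized patient in shock or in the ICU with a rate of 30 or less.

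| Section | Requirement | Where the patient falls |
|---|---|---|
| Clinical Assessment Protocol | severe = R and C, otherwise mild/moderate | mild/moderate |
| Timeline and Figure 1, T-branch | mild/moderate and not hospitalized | not T (hospitalized) |
| Timeline and Figure 1, D-branch | severe/critical and hospitalized | not D (not severe by the written rule) |
| Figure 2 | hospitalized group is moderate to severe | in the hospitalized group |
| Metabolomic Profiling | D-branch = severe | depends on branch, which is undefined for this patient |
| Statistical Analysis | severe vs nonsevere | not stated |

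The definitions cannot all hold for this patient.

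**Step 3. The plan's own sample size.** Inputs from Sample Size Calculation: p1 = 0.20, p2 = 0.05, two-sided alpha 0.05 (as I read its 95% significance level), power 0.80, ratio 1. With the mean proportion p̄ = 0.125,

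n per group = [1.96·√(2·p̄(1−p̄)) + 0.842·√(p1(1−p1) + p2(1−p2))]² / (p1−p2)² = 75.1, so 76 per group or 152 in total.

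With continuity correction it is 88 per group or 176 in total. Neither is 200, so 200 is more than these inputs need. The point here does not depend on this. It only means that the illustration starts above 80% power.

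**Step 4. Illustration if the written rule governs.** Assume 100 truly severe patients (20% with elevated TNF-α) and 100 truly mild ones (5%). Move k of the severe patients into the mild/moderate group, and assume that their rate is also 20%:

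- severe group: 100 − k patients, rate 20%
- mild/moderate group: 100 + k patients, rate (5 + 0.20k)/(100 + k)

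For k = 20 the comparator rate is 9/120 = 7.5%. For k = 40 it is 13/140 = 9.3%. Exact power of the two-sided 5% chi-square test:

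| Severe patients moved | Group sizes | Comparator rate | Difference (points) | Power |
|---|---|---|---|---|
| 0% | 100/100 | 5.0% | 15.0 | 92% |
| 5% | 95/105 | 5.7% | 14.3 | 88% |
| 10% | 90/110 | 6.4% | 13.6 | 84% |
| 20% | 80/120 | 7.5% | 12.5 | 74% |
| 40% | 60/140 | 9.3% | 10.7 | 55% |

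The normal approximation gives 90%, 86%, 82%, 73% and 55% for the same rows, so the pattern does not depend on the method.

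**The case against.** The strongest reply is that branch, not the written severity rule, may be the operative grouping. Metabolomic Profiling equates branch with severity, and Results counts enrolment by branch (30 T, 85 D). If so, a ventilated or ICU patient, being hospitalized, sits on the severe side and the dilution does not arise. This stands as a limit on the conclusion. A reader might infer that such patients will be analysed as mild/moderate; the document does not establish that, because it does not say which rule prevails. That silence is itself the remaining defect.

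Other points also stand in part:

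- The rule does not say when the respiratory rate is measured. Figure 1 describes patients referred to the emergency room, so a presenting value may be meant. That could reduce the number affected, but patients with shock or ICU admission and a rate of 30 or less would remain.
- The share moved is unknown. At 5% to 10%, power in the illustration stays at 88% to 84%, above the planned 80%. The 100/100 set-up is also not the enrolment reported so far.
- Dilution assumes that the misplaced patients have biomarker levels like those of other severe patients.
- It would be too strong to call severity the study's only grouping variable: time points and healthy donors or volunteers are also compared.

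That the article condenses a fuller protocol is no answer to the main point. The rule is not omitted; it is stated, with an explicit default, and it conflicts with other sections.

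**Conclusion.** The point holds as a defect of definition. As written, a respiratory rate above 30 is necessary for severe status, patients with organ support, shock or ICU admission can default to mild/moderate, and this does not agree with the hospitalization-based branches or the Figure 2 legend. The severe and nonsevere analysis groups are therefore not uniquely defined. This follows from the text alone and needs no numerical assumption.

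The consequence is conditional. If the written rule forms the groups, differences would tend to be diluted and ROC cutoffs distorted, provided that the misplaced patients resemble other severe patients. In the illustration, power drops below the planned 80% somewhere between 10% and 20% misplaced. That range is not an estimate for this study, because the document gives no share. If the branch forms the groups, these patients would sit on the severe side, and what remains is the contradiction between sections.

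**What to change.** Before analysis starts:

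1. Reconcile Clinical Assessment Protocol, Timeline, the Figure 1 and Figure 2 legends, Metabolomic Profiling and Statistical Analysis into one analysis classification based on day-0 data.
2. Correct the coupling wording so that patients with organ support, shock or ICU admission do not fall into mild/moderate by default. The criteria themselves are for the investigators to set.
3. State in Statistical Analysis whether this classification or the T/D branch defines the severe and nonsevere groups.
4. Apply the rule to every patient, including the 115 already enrolled (30 + 85).

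The cost is a wording change and one re-run of the classification. Results says that data analysis is to start only after all inclusion data are collected, so there is time, although the thromboelastometry branch is already being analysed and should be checked against the same rule. It cannot be assumed that the recorded data suffice: Table 1 lists oxygen saturation, supplementary oxygen and mechanical ventilation, but not respiratory rate, PaO2/FiO2, shock or ICU admission. Some chart retrieval may be needed.

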**Symptoms**
Fever, chills, sneezing, sore throat, headache, cough, coryza, anosmia, dysgeusia, diarrhea, asthenia, nausea, vomit, dizziness, and others
**Comorbidities**
Pulmonary chronic disease, chronic cardiopathy, hypertension, diabetes, chronic kidney disease, pregnancy, neoplasms, smoking, alcohol ingestion, psoriasis, immunodepression, HIV, Dengue, hanseniasis, Zika virus, chikungunya, Chagas disease, yellow fever, leishmaniasis, malaria, H1N1, and others
**Previous medications**
Angiotensin converting enzyme inhibitors, angiotensin II receptor antagonists, nonsteroidal anti-inflammatory drugs, and others
**Treatments aimed at COVID-19**
Clinical support, dexamethasone, enoxaparin, chloroquine, antibiotics, ivermectin, nitazoxanide, lopinavir, ritonavir, remdesivir, immunoglobulin, plasmapheresis, anti-IL6, JAK inhibitor, and others

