### Assessment of Molecular and Cellular Immunological Biomarkers

Serum biomarkers will be assessed using the Luminex Bio-Plex Pro platform set for 27 human immune mediators (Bio-Rad Laboratories, California) for the simultaneous assessment of the following analytes: chemokines (CXCL8, CCL11, CCL3, CCL4, CCL2, CCL5, and CXCL10), proinflammatory cytokines (IL-1β, IL-6, TNF-α, IL-12p70, IFN-γ, IL-17A, and IL-15) and regulatory cytokines (IL-1Ra, IL-4, IL- 5, IL-9, IL-10, and IL-13), and cell growth factors (IL-2, IL-7, FGF-basic, PDGF, VEG, G-CSF, and GM-CSF). All procedures will follow the manufacturer’s recommendations, with levels obtained at days 0, 3, and 9.

The expression levels of immune mediators will be assessed by TaqMan quantitative RT-PCR (qRT-PCR) assays (Applied Biosystems, Foster City, CA) for each transcript, with retro-transcription set up with 1 ng/μL of RNA from PBMCs and from neutrophils. The reactions will be carried out on a QuantiStudio 3 Thermal Cycler (Applied Biosystems, CA) in standard mode [26]. Alternatively, qRT-PCR experiments for selected genes will be based on the SYBR Green (family of dyes for molecular biology) detection methodology using the SYBR Green PCR Master Mix and universal cycling conditions on the ABI Prism 7000 Sequence Detection System. Expression levels will be assessed on days 3 and 9.

Immunophenotypic/functional profiles of circulating leukocytes will be assessed upon short-term culture in vitro. The cell suspension will be stained with distinct panels of monoclonal antibodies comprising CD3, CD4, CD8, HLA-DR, CD25, CD19, CD5, CD27, CD38, PD-1, CD28, CD14, CD16, and CD56 for cell surface analysis, and IL-1β, IL-6, TNF-α, IFN-α, IL-5-PE, and IL-10 for evaluation of intracytoplasmic functional status. Cells will be run on a FORTESSA flow cytometer (BD Bioscience, CA). An average of 100,000 cells will be analyzed per sample. The phenotypic/functional parameters will be assessed using FlowJo software (BD, New Jersey). Leukocyte phenotyping will be obtained at days 0, 3, and 9.

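### Biomarker contrasts and ROC cutoffs do not separate samples drawn after anti-IL6, JAK-inhibitor or dexamethasone treatment, so day-9 and within-D-branch results for IL-6 and Th17-type cytokines can mix therapy with disease

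*Protocol article*

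**What the plan says.** **Treatments.** The list of treatments aimed at COVID-19 in Textbox 1 contains dexamethasone and ends with "remdesivir, immunoglobulin, plasmapheresis, anti-IL6, JAK inhibitor, and others". Table 1 registers COVID-19 treatment at days 0, 3, 9 and 18.

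**Their action, in the article's own words.** The Introduction describes "tocilizumab, an IL-6 receptor-blocking humanized antibody used to treat rheumatoid arthritis" and says that the JAK inhibitor baricitinib "reduces Th17-type cytokine secretion by blocking AP2-associated protein kinase 1". It introduces tocilizumab as one of the other anti-inflammatory treatments, directly after dexamethasone.

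**What is measured.** The serum panel includes "IL-1β, IL-6, TNF-α, IL-12p70, IFN-γ, IL-17A, and IL-15", "with levels obtained at days 0, 3, and 9". Table 1 places neutralizing antibodies at day 18 only.

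**Who is sampled when.** Under Timeline, the D-branch is the hospitalised severe/critical group and the T-branch is not hospitalised. Only the D-branch has a day-3 visit. Biological Samples ties day 0 to inclusion and does not require it to precede treatment.

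**Analysis.** "To compare mean values of soluble biomarkers between groups", Statistical Analysis names the t test or ANOVA, or the Mann-Whitney or Kruskal-Wallis test. It also compares successive time points and sets ROC cutoffs for progression. Treatment appears only as a profile to be compared between the groups.

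**A contrast within the article.** Recruitment excludes anticoagulant users for the coagulation tests. No corresponding rule covers treatments that act on the immune analytes.

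**The concern.** Some of the recorded treatments act on the quantities being measured. If they are given mostly to one branch, a day-9 difference between branches may be partly a treatment effect. The same holds for a change inside the D-branch from day 0 to day 3 or day 9.

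The ROC step carries the problem further. The Discussion presents the biomarkers as prognostic tools. A cutoff built partly on post-dose samples may pick out patients who were treated and not patients who will deteriorate. IL-6 is exposed most directly. The Introduction also links IL-1β, IL-6 and TNF-α to the Th17-type response, and TNF-α is the analyte on which the sample size rests.

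**Working it through.** **1. What the plan fixes, contrast by contrast**

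| Contrast | Exists in the plan? | Can it mix therapy with disease? |
|---|---|---|
| Day 0, D against T | Yes | Less likely, but day 0 is not defined as pre-treatment |
| Day 3, D against T | No; day 3 is D-branch only | Not applicable |
| Day 9, D against T | Yes | Yes |
| D-branch change, day 0 to days 3 and 9 | Yes | Yes |
| ROC cutoffs | Yes; visit not stated | Yes, if days 3 or 9 are used |
| Day 18 neutralizing antibodies, D against T | Measured; no test named | Only if such a comparison is made |

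**2. Figures available.** The article gives neither the share of patients treated nor the effect of treatment on any analyte, so there is no plan figure on this point to reproduce. The stated total of 200 at a 1:1 ratio supplies 100 per branch for the illustrations below. (The stated inputs, 20% against 5%, two-sided 0.05 and 80% power, give 76 per group, or 152 in total, without continuity correction, and 176 with it. At 100 per group the power is 0.90. That is a separate matter and does not bear on this point.)

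**3. A false difference, parametric test.** Assume no true disease difference, unit SD, and a share f of the D-branch shifted by s SD.

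- Mean shift: m = f·s
- D-branch variance: v = 1 + f(1 − f)s²
- Standard error: SE = √(v/100 + 1/100)
- Rejection probability: Φ(m/SE − 1.96) + Φ(−m/SE − 1.96)

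Example, f = 0.20 and s = 2: m = 0.40, v = 1 + 0.16 × 4 = 1.64, SE = √0.0264 = 0.1625, m/SE = 2.46, rejection probability 0.692.

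| Share treated (assumed) | s = 1 | s = 2 | s = 3 |
|---|---|---|---|
| 5% | 0.064 | 0.104 | 0.161 |
| 10% | 0.106 | 0.256 | 0.432 |
| 20% | 0.275 | 0.692 | 0.899 |
| 40% | 0.762 | 0.996 | 1.000 |

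The nominal level is 0.05.

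**4. A false difference, rank test.** Mann-Whitney limits the effect of extreme values. In the worst case every treated D-branch value ranks above all T-branch values, and P(D > T) = 0.5 + f/2, which is 0.525, 0.55 or 0.60 at f = 5%, 10% or 20%. The null standard error with 100 per branch is √(201/(12 × 100 × 100)) = 0.0409. The shifts are then 0.025/0.0409 = 0.61, 0.05/0.0409 = 1.22 and 0.10/0.0409 = 2.44 standard errors. The expected statistic reaches 1.96 at f = 2 × 1.96 × 0.0409 = 0.16. The rank test therefore reduces the problem at low exposure and does not remove it at 20%.

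**5. The opposite direction.** Take the planning rates of 20% against 5%, and let treated D-branch samples read at the 5% rate. The D-branch rate is 0.20(1 − f) + 0.05f, which is 0.1925, 0.185, 0.17 and 0.14 at f = 5%, 10%, 20% and 40%. Power with 100 per branch falls from 0.90 to 0.88, 0.85, 0.78 and 0.58.

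**The case against.** **A short article need not give every analysis rule.** Handling of post-treatment samples often sits in a SAP, and none is shown. Treatment is recorded at every visit, so samples could be separated later. This has weight. However, the article does name the between-group tests, the successive-day comparisons and the ROC step, and it writes an interference rule for coagulation alone. As stated, those analyses make no distinction.

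**Exposure is not shown.** Textbox 1 is a recording list and does not show that any participant received these drugs. The Introduction describes tocilizumab as compassionate use in China and Italy, and baricitinib as under evaluation. A reader might infer that exposure falls almost only in the D-branch, leaving adjustment with no overlap. The article gives no use by branch, so concentration there is only a reasonable inference.

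**The direction and multiple of the IL-6 change are not given.** A reader might infer that receptor blockade raises serum IL-6 several-fold. The Introduction states the blockade and says nothing about the serum level afterwards.

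**Neutralizing antibodies.** A reader might infer that the day-18 comparison is distorted by immunoglobulin or plasmapheresis. Statistical Analysis names no test for neutralizing antibodies, and the article does not say that the listed immunoglobulin carries neutralizing antibody. Only a conditional request is justified.

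**Restriction selects on severity.** Dropping post-dose samples probably removes the sickest patients. This objection stands, and it is why the restricted analysis should accompany the full one and not replace it.

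**Conclusion.** The point holds for the day-9 between-branch contrasts, for D-branch changes from day 0 to days 3 and 9, and for the ROC cutoffs, all for IL-6 and the Th17-type cytokines. It does not extend to a day-3 contrast between branches, because none exists.

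The documents do not determine the size. Under the assumptions shown (100 per branch, 5-40% of the D-branch treated, shift of 1 to 3 SD), therapy alone would make a branch difference significant in 6% to nearly 100% of studies. In the masking direction, power falls from 90% to between 88% and 58%. If use was rare, the effect is small. Dexamethasone belongs with the other two classes: a sample taken before anti-IL6 or a JAK inhibitor may still follow a corticosteroid.

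The change is worth making because it is cheap, and because the Results section says that data analysis starts only after all inclusion data are collected.

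**What to change.** Add to Statistical Analysis:

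- Each sample is flagged as before or after first dose of anti-IL6, JAK inhibitor or dexamethasone, using the treatment data already registered at each visit plus a first-dose date.
- For IL-6 and the Th17-type cytokines, the day-0 severity contrast is presented in pre-dose samples.
- For the same analytes, the day-9 contrasts, the D-branch changes from day 0 and the ROC cutoffs are reported twice: with all samples, and with pre-dose or unexposed samples only. Post-dose samples are shown as a separate stratum.
- If day-18 neutralizing antibodies are compared between branches, that comparison is shown with and without recipients of immunoglobulin or plasmapheresis.

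**Cost.** Analysis wording and one date field, with no change to care or sampling. The restricted set is smaller and probably omits the sickest patients, so it is reported beside the full set.
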